### Outcome measures and methods

2.7

#### Primary outcome

2.7.1

The primary outcome, the change in the maximum diameter (ΔD) of the pGGN from baseline, which will be calculated using the following formula:

ΔD=Bmax−Pmax

Where: *Bmax* = baseline maximum diameter and *Pmax* = post-treatment maximum diameter.

Measurements will adhere to the 2017 Fleischner Society guidelines for pulmonary nodule assessment (16). For participants with multiple nodules, the maximum diameter of the nodule with the highest risk or the largest size will be measured. In cases where multiple nodules share an identical maximum diameter, the nodule will be selected for measurement following risk stratification, prioritizing the highest-risk nodule. The analysis of CT images will be conducted by two independent board-certified radiologists, each possessing relevant clinical expertise. Using lung window settings (window width: 1400 HU; window level: −700 HU), the pGGN will be identified, and its maximum diameter will be measured on the transverse slice where it appears largest. Triplicate measurements will be conducted for each nodule at each time point, and the average value will be calculated and recorded in millimeters (mm), rounded to the nearest integer. Assessments will be performed at baseline, at 3 months (end of treatment), and at 1 year (end of follow-up).

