### Sample size calculation

2.9

The primary outcome was the difference in changes in the maximum diameter of pGGNs before and after treatment. Based on preliminary pre-experimental results showing mean ± standard deviation (SD) differences of 1.11 ± 2.12 mm (intervention group) and 0.19 ± 1.25 mm (control group), sample size was determined using PASS software (version 2021). With a two-sided *α* = 0.05, 1-*β* = 0.90, 1:1 allocation ratio, and accounting for an anticipated 10% dropout rate, a minimum of 86 participants per group is required.

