### Minimal clinically important difference (MCID)

2.10

This study prioritizes the MCID over mere statistical significance to assess clinical relevance of the primary outcome. Using a distribution-based method, the MCID is calculated as 0.5 times the SD. By incorporating findings from preliminary pilot data and aiming to eliminate variability that may be attributed to the treatment effect itself, the SD of changes in the pGGN maximum diameter in the control group was used, setting the MCID threshold at 0.63 mm.

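### Rounding the mean of three diameter readings to whole millimetres adds avoidable noise to the primary outcome; the cost is modest and nearly free to remove

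*Protocol article*

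**What the plan says.** All references are to the protocol article.

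- **Section 2.7.1 (Primary outcome).** The endpoint is "The primary outcome, the change in the maximum diameter (ΔD) of the pGGN from baseline", formed as the baseline minus the post-treatment maximum diameter. Three readings are taken of every nodule at every visit. The rule for combining them is that "the average value will be calculated and recorded in millimeters (mm), rounded to the nearest integer". Diameters are assessed at baseline, 3 months and 1 year, and the section refers to a published measurement guideline.
- **Section 2.9 (Sample size).** The pilot data are given as "differences of 1.11 ± 2.12 mm (intervention group) and 0.19 ± 1.25 mm (control group"), a planned difference of 0.92 mm. With two-sided alpha 0.05, 90% power and 10% dropout, the stated need is 86 per group.
- **Section 2.10 (MCID).** "the MCID is calculated as 0.5 times the SD" of the control-arm change, "setting the MCID threshold at 0.63 mm".
- **Section 2.7.2.2 (Long-term secondary outcomes).** The reduction rate uses the same two diameter symbols and is cut at 25% and 50% to form response categories. The Mayo risk formula takes nodule diameter in mm.
- **Section 2.14 (Statistical analysis).** Change in diameter is analysed in a linear mixed model with baseline diameter as a covariate.

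The article does not say that the unrounded mean, or the three single readings, will be kept for analysis.

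**The concern.** Averaging three readings is done to reduce measurement error. Rounding the average to an integer then puts a new error back into each recorded diameter. Two rounded diameters enter every change score, so the error enters the primary outcome twice. A rounded baseline also enters the model as a covariate.

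The recording unit of 1 mm is large relative to the control-arm SD of change, 1.25 mm, so the added variance is not negligible. What is at stake is some precision on the primary comparison, and some switching of participants between response categories near the 25% and 50% cut-points. An analysis plan written later could not restore decimals that were never recorded.

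**Working it through.** **Inputs from the article.** Difference 1.11 − 0.19 = 0.92 mm; SDs of change 2.12 (CJG) and 1.25 (control); two-sided alpha 0.05; power 0.90; 1:1 allocation; dropout 10%; 86 per group; MCID 0.63 mm; recording unit 1 mm.

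**Assumptions.** Rounding error is uniform over ±0.5 mm and roughly independent between visits. The article does not say whether the pilot SDs came from rounded diameters, so both cases are shown.

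**1. The plan's own figures.**
- Variances: 2.12² = 4.4944 and 1.25² = 1.5625, sum 6.0569.
- A Welch t-test (noncentral t) needs 77 evaluable per arm, with power 90.2%. Then 77 / 0.9 = 85.6, so 86 per group. The stated sample size is reproduced.
- MCID: 0.5 × 1.25 = 0.625, stated as 0.63. Reproduced.

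**2. Variance added by rounding.**
- Uniform error with a 1 mm unit: variance 1/12 = 0.083 mm² per recorded diameter.
- The change score has two: 2 × 1/12 = 1/6 = 0.167 mm², SD √0.167 = 0.41 mm.
- Simulation with assumed baselines (mean 8 mm, SD 1.5 to 3 mm) gave 0.166 to 0.170 mm².
- Relative to the pilot variances: 0.167 / 1.5625 = 10.7% (control), 0.167 / 4.4944 = 3.7% (CJG), and 0.333 / 6.0569 = 5.5% of the sum.

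**3. Effect on power** (Welch, 77 evaluable per arm, difference 0.92 mm).

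| Case | SDs with rounding | Power with rounding | SDs without rounding | Power without rounding |
|---|---|---|---|---|
| Pilot SDs unrounded | 2.16, 1.31 | 88.7% | 2.12, 1.25 | 90.2% |
| Pilot SDs already contain rounding | 2.12, 1.25 | 90.2% | 2.08, 1.18 | 91.7% |

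In the first case the standard error of the difference rises from √(6.0569/77) = 0.280 to √(6.3902/77) = 0.288 mm. Keeping 90% power with rounding would take 81 evaluable, or 90 per group. In the second case 86 per group already covers the rounding; without it, 73 evaluable (82 per group) would give 90%. Either way rounding costs about 1.5 points of power, equivalent to about 4 evaluable participants per arm.

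**4. Effect on the mean.** In simulation the group mean changes moved by less than 0.001 mm.

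**5. Effect on response categories, if these use the recorded diameter.** With baselines assumed uniform on 6 to 10 mm and normal changes with the pilot means and SDs (2 million draws per arm), about 4% of control and 8% of CJG participants fall in a different category from the one given by the unrounded mean.

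**6. Individual changes against 0.63 mm.** Under the same assumptions, about 5% (CJG) and 8% (control) land on the other side of 0.63 mm after rounding. A true reduction of exactly 0.63 mm is recorded as 0 mm in 37% of cases and as 1 mm in 63%.

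**The case against.** **The MCID and the planned effect are group-level quantities.** A reader might infer that a trial recording whole millimetres cannot resolve a 0.63 mm MCID or a 0.92 mm effect. The article does not support that. Section 2.10 uses the MCID to judge the primary outcome, and section 2.14 analyses that outcome as a between-group comparison in a mixed model. Averages of integer records estimate a difference well below 1 mm without material bias. This objection stands in full.

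**No participant is classified against the MCID.** No section plans a responder analysis at 0.63 mm, so the 5% and 8% in step 6 matter only if the MCID is applied to individuals, which the article does not say. This also stands.

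**The power loss may already be covered.** If the pilot SDs came from rounded diameters, the planned 90% holds. The Welch calculation is also only a proxy for a baseline-adjusted mixed model. Both points limit the size of the finding. Neither makes the rounding free, since unrounded data would then give more than 90%.

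**The unrounded mean is not the truth.** The Discussion acknowledges scanner and reader variability, and the article gives no reader-error figure. The category changes are therefore disagreements with the unrounded mean, not errors against a true diameter. That is correct, but rounding adds to whatever reader error exists.

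**The rounding may follow the cited guideline.** This cannot be checked from the article. A reporting convention would not stop the trial from keeping the unrounded mean for analysis. It is also possible that the full case report form keeps the single readings; the article does not say.

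**Conclusion.** The point holds as a modest efficiency loss. The article fixes a rule that rounds an already computed mean before the primary change score is formed. This adds about 0.167 mm² per change score and costs about 1.5 points of power at 77 evaluable per arm. Whether that takes the trial below its planned 90% depends on the unstated rounding status of the pilot SDs.

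The reduction rate, response categories and Mayo score inherit the rounding if they use the recorded diameter. The 4% to 8% change of response category rests on assumed 6 to 10 mm baselines and normal changes; the eligibility criteria set no diameter limits.

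This is neither a bias nor an error in the sample size, and it does not threaten the primary conclusion. It is worth changing because the better option costs almost nothing.

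**What to change.** In section 2.7.1 and on the case report form, record each of the readings and the per-visit mean to at least 0.1 mm. Compute the change in diameter, the baseline covariate, the reduction rate, the response category and the Mayo risk from the unrounded mean. Round only for display, or where a reporting convention calls for whole millimetres.

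The cost is one field format and one sentence, with no extra readings or participants. The change is best made before baseline values are recorded; section 2.13 anticipates recruitment from September 2025. If recruitment has begun, unrounded values can be recovered only where the single readings were kept or the scans are read again.

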#### Secondary outcomes

2.7.2

##### Short-term secondary outcomes

2.7.2.1

Psychological Status: Anxiety will be assessed utilizing the Beck Anxiety Inventory (BAI), with scores categorized as follows: 0–9 (minimal/no anxiety), 10–18 (mild anxiety), 19–29 (moderate anxiety), and 30–63 (severe anxiety) (17). Depression will be evaluated using the Beck Depression Inventory-II (BDI-II). Scores were classified as: 0–13 (minimal/no depression), 14–19 (mild depression), 20–28 (moderate depression), and 29–63 (severe depression) (18). Assessments will be performed at baseline and post-treatment.Quality of Life: Will be measured via the 36-item Short Form Health Survey (SF-36), a self-reported instrument assessing nine domains: physical functioning, role limitations due to physical health, bodily pain, general health perceptions, vitality, social functioning, role limitations due to emotional problems, mental health, and health change. Scores range from 0 to 100, with higher scores indicating better quality of life (19). Assessments will be performed at baseline and post-treatment.Medication Adherence: The adherence rate for CJG will be calculated using the formula: (Actual dose / Prescribed dose) × 100%. Patients will be categorized into three adherence groups: <80%, 80–120, and >120%. The count and percentage of cases in each group will be examined.

##### Long-term secondary outcomes

2.7.2.2

Reduction rate of the maximum nodule diameter: the reduction rate will be calculated as:

$$\frac{\left(\text{Bmax}-\text{Pmax}\right)}{\text{Bmax}}\times 100$$

Where: *Bmax* = baseline maximum diameter and *Pmax* = post-treatment maximum diameter.

Assessments will be performed at 3 months (treatment completion), and 1 year (follow-up completion). According to the *Guidelines for Clinical Research of New Traditional Chinese Medicine Drugs*: complete response (CR): complete resolution of the nodule on chest CT; partial response (PR): > 50% reduction in maximum diameter; stable disease (SD): 25–50% reduction in maximum diameter; progressive disease (PD): < 25% reduction or increase in maximum diameter (20).

Nodule density: In the CT lung window, the largest pGGN will be identified, and an experienced radiologist will measure the density in the central 60–80% of the slice showing the nodule’s largest area, avoiding vessels, bronchi, and pleura. The average of these three measurements will be calculated and recorded as the final density value for that time point. This evaluation will be performed at baseline, 3 months, and 1 year.Malignant risk of pulmonary nodules: Use the Mayo model formula: Probability = e^x^/(1 + e^x^), where e is approximately 2.718, and x = −6.8272 + (0.0391 × age) + (0.7917 × smoking history) + (1.3388 × tumor history) + (0.1274 × nodule diameter) + (1.0407 × spiculation) + (0.7838 × location) (21). Smoking, tumor history, spiculation, and upper lobe location are binary (1 if present, 0 if not), and nodule diameter is in mm. For multiple nodules, use the highest risk nodule. Assessments will occur at baseline, 3 months, and 1 year.

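### The secondary response categories class unchanged nodules, and nodules that shrink by less than 25%, as progressive disease, and no category identifies growth

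*Protocol article*

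**What the plan says.** Section 2.7.2.2 (Long-term secondary outcomes) defines the reduction rate as (Bmax − Pmax)/Bmax × 100, assessed at 3 months and at 1 year. It then sorts patients into four classes, attributed to a cited guideline for clinical research on new TCM drugs. The top class is disappearance of the nodule, and a partial response needs the diameter to fall by more than half. The class below that is given as "stable disease (SD): 25–50% reduction in maximum diameter". Every remaining patient goes into the lowest class, which the article words as "progressive disease (PD): < 25% reduction or increase in maximum diameter".

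Section 2.9 (Sample size calculation) plans on mean changes of "1.11 ± 2.12 mm (intervention group) and 0.19 ± 1.25 mm (control group"). Section 2.10 works from the control-arm standard deviation, "setting the MCID threshold at 0.63 mm". Section 2.7.1 records diameters to the whole millimetre. Section 2.14 compares categorical variables by chi-square or Fisher's exact test.

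**The concern.** The labels do not match the bands. Zero change is below a 25% reduction, so an unchanged nodule is progressive; so is one that has shrunk by 20%. To be called stable, a nodule must have lost at least a quarter of its diameter. Growth has no class of its own.

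This also conflicts with the article's own vocabulary. The Abstract, Introduction and Discussion use the word stable for nodules managed by surveillance, not for nodules that have shrunk by a quarter. The Introduction uses progression for the move from an indolent phase into growth.

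At stake is the meaning of the published category rates. These four classes carry the names of oncology response categories, and readers will take the progressive share as the share that grew. If CJG turned some growing nodules into unchanged ones, this table would not show it, because both kinds sit in the same class.

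**Working it through.** **The planning figures.** The first step is to confirm that the section 2.9 means and standard deviations are the ones the trial is sized on.

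- Inputs: difference 1.11 − 0.19 = 0.92 mm; standard deviations 2.12 and 1.25 mm; "With a two-sided *α* = 0.05, 1-*β* = 0.90"; 10% dropout.
- Normal approximation: n = (1.960 + 1.282)² × (2.12² + 1.25²)/0.92² = 10.51 × 6.057/0.8464 ≈ 75.2, so 76 per group.
- With the noncentral t distribution, n = 77 per group, and 77/0.9 = 85.6, rounded up to 86. This matches the stated 86.

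**Where the planned benefit falls.** A shrinkage of d mm is classed as progressive when d < 0.25 × B, that is, when the baseline diameter B exceeds d/0.25.

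- Planned mean CJG change: 1.11/0.25 = 4.44 mm.
- MCID: 0.63/0.25 = 2.52 mm.
- A recorded shrinkage of 1 mm is 20% of a 5 mm nodule, so it is progressive for any recorded baseline of 5 mm or more.

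**Share labelled progressive.** The article states no minimum, maximum or mean baseline diameter, so B is an assumption. With normally distributed changes and B fixed, the share labelled progressive is Φ((0.25B − mean)/standard deviation). The share with actual growth is Φ(−mean/standard deviation): Φ(−1.11/2.12) = 30% for CJG and Φ(−0.19/1.25) = 44% for control, at every B. The difference between the two is the share labelled progressive without growth.

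| Assumed B (mm) | Progressive, CJG | Progressive, control | Progressive without growth, CJG | Progressive without growth, control |
|---|---|---|---|---|
| 4 | 48% | 74% | 18% | 30% |
| 5 | 53% | 80% | 23% | 36% |
| 6 | 57% | 85% | 27% | 41% |
| 8 | 66% | 93% | 36% | 49% |
| 10 | 74% | 97% | 44% | 53% |
| 15 | 89% | 99.8% | 59% | 56% |

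Worked line for B = 8, where the threshold is 2 mm: CJG Φ((2 − 1.11)/2.12) = Φ(0.42) = 66%; control Φ((2 − 0.19)/1.25) = Φ(1.45) = 93%.

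**Effect of whole-millimetre recording.** At a recorded baseline of 8 mm, a recorded shrinkage of 2 mm is exactly 25% and counts as stable, so the progressive class needs a recorded change of 1 mm or less. Treating the change itself as rounded puts the cut at 1.5 mm:

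- CJG: Φ((1.5 − 1.11)/2.12) = 57%.
- Control: Φ((1.5 − 0.19)/1.25) = 85%.
- Progressive without recorded growth (change between −0.5 and 1.5 mm): CJG 57.3% − 22.4% ≈ 35%; control 85.3% − 29.1% ≈ 56%.

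Across 5–10 mm, rounding gives 57–74% for CJG and 85–97% for control. The 8 mm figures fall noticeably, but the overall picture does not change.

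**The case against.** The strongest reply is that little depends on these labels. The primary outcome is the signed change in diameter, in which growth is negative, measured at baseline, 3 months and 1 year and analysed with a linear mixed model. The continuous reduction rate keeps its sign too. A reader might infer that the trial cannot detect harm or prevention of growth. The article does not support that; the blind spot is confined to the four-way grouping. The progressive label also triggers nothing in section 2.5, where ending efficacy follow-up depends on criteria for surgery or a cancer diagnosis.

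Other parts of the reply also stand:

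- The bands are attributed to a guideline that is not at hand. That may explain the cut-offs, but it does not change what the printed labels convey.
- Progressive versus the rest is in effect a contrast on at least 25% shrinkage, and it does separate the arms: by about 22–28 percentage points at 6–10 mm in the unrounded calculation. The cut-off works as a comparison. The fault lies in the names and in the missing growth class.
- A reader might infer that most of both arms will be called progressive whatever the nodule size. For CJG that holds only above about 4.44 mm; at 4 mm the share is 48%.
- The same labels apply at 1 year, but the planning inputs describe change over treatment, so no 1-year percentages can be derived.
- It would be too strong to say that no change is the expected course. The Introduction calls these nodules indolent but also reports that more than half progress during follow-up.

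**Conclusion.** The point holds as a labelling defect in one categorical secondary outcome. That an unchanged or modestly shrunken nodule is reported as progressive, and that growth has no class, follows from the printed definitions without any assumption. The 4.44 mm and 2.52 mm thresholds follow from the article's own figures.

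The percentages are illustrative. They rest on an assumed baseline of 5–10 mm, normally distributed changes with the pilot means and standard deviations, and the 3-month time point. Within that range, roughly 43–60% of the CJG patients called progressive (23/53 to 44/74) and 45–55% of the control patients so called (36/80 to 53/97) would have had no growth.

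The primary analysis, the continuous reduction rate and the sample size are sound on this point. It should be fixed, because the published rates would otherwise be misread, but it does not put the trial's main conclusion at risk.

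**What to change.** First, check the labels and cut-offs in section 2.7.2.2 against the cited guideline. Then take one of two routes:

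1. Redefine stable disease as no material change in either direction, and progressive disease as an actual increase beyond a limit set in advance.
2. Keep the bands under neutral names that state the reduction (for example, at least 25% versus less than 25%), and report growth as a separate category.

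Make the change before unblinding, since redefining progression afterwards would look data-driven. The cost is wording in the protocol and analysis plan: every category derives from diameters already measured, and the tests in section 2.14 can stay as they are. Under the first route, the rates become less directly comparable with studies that use the same bands; a supplementary table on those bands would cover this.

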#### Safety outcomes

2.7.3

Safety outcomes will be evaluated through the continuous surveillance of adverse symptoms and physical signs, supplemented by a comprehensive analysis of all scheduled laboratory tests and electrocardiograms (ECGs) conducted during study visits. Specifically, symptoms and signs will be monitored at each patient interaction, including both scheduled visits and any unscheduled communications. Laboratory and ECG safety parameters will be evaluated at baseline, 3 months following the intervention or at the time of early withdrawal, and 1-year observational period after treatment. Additionally, participants who reports symptoms suggestive of a potential adverse reaction during the course of the drug administration will be subjected to immediate unscheduled laboratory testing as clinically indicated. All adverse medical events will be meticulously documented in Case Report Forms (CRFs) within 24 h of occurrence, detailing clinical presentations, time of onset, duration, severity (graded according to CTCAE v5.0), interventions, outcomes, and causality assessment in relation to the trial drug. Trial termination will be considered when participants required additional concomitant medications, surgical interventions, or other physical therapy targeting pulmonary nodules.

#### Exploratory outcomes

2.7.4

To explore the potential mechanisms by which CJG may treat pGGNs, a longitudinal biospecimen collection protocol has been established. Paired saliva and feces samples will be collected at baseline, mid-term (months 1 and 2), and end (month 3) of CJG treatment. For saliva, participants will fast for 2 h, rinsed their mouths, and collected 2–3 mL of unstimulated saliva by drooling into a sterile tube, which will then be frozen on dry ice and stored at −80° C. For feces, participants will collect approximately 5 g at home using sterile tools, avoiding air exposure and toilet water. These samples will be initially kept at −20° C and later transferred on ice to a central lab for storage at −80° C.

After assessing sample quality, total genomic DNA from microbial communities will be extracted. The V3-V4 regions of 16S rRNA will be amplified for high-throughput sequencing. Sequences will be preprocessed through filtering, denoising, and chimera removal, resulting in amplicon sequence variants (ASVs) for bioinformatic investigations. This will include *α*-diversity analysis with Shannon and Chao1 indices, *β*-diversity exploration using principal coordinate analysis (PCoA) with Bray-Curtis distance, genus-level species differentiation via Linear discriminant analysis Effect Size (LEfSe), and examining the relationship between microbial genus abundance and time using multivariate linear association (MaAsLin).

Metabolites were extracted from saliva and feces using a chilled methanol–water solution. After centrifugation, the supernatant was analyzed by LC–MS. The raw data were processed for peak alignment, de-noising, and normalization. Multivariate statistical analyses, such as principal component analysis (PCA), partial least squares discriminant analysis (PLS-DA) and orthogonal PLS-DA (OPLS-DA), identified differential metabolites (VIP > 1 and *p* < 0.05). Kyoto encyclopedia of genes and genomes (KEGG) enrichment analysis revealed altered pathways. The Benjamini-Hochberg method was used to calculate the false-discovery rate (FDR) for multiple comparisons, with significance set at *P*_FDR_ < 0.05.

